## 1. Abstract

Hospital-associated functional decline is a common, costly, and important event in the health trajectory of older adults. Mobility has been identified as a potential mediator for many of these outcomes. In this study, we will use wearable devices to monitor patients' physical activity during inpatient admission on floors with and without nursing mobility protocols that provide guidance on recommended activity. This is part of a health system initiative to deploy a hospital-based mobility protocol across the entire system over time. Upon discharge, we will measure each patient's baseline level of physical activity and then randomly assign them to 3 months of passive monitoring or a social incentive-based gamification intervention with personalized step goals to increase activity. We will monitor patient outcomes and conduct regular validated surveys on patient function.

## 2. Overall objectives

The primary objective is to assess the effectiveness of a social incentive-based gamification intervention to increase physical activity in the 3 months after hospital discharge. We will explore patients' physical activity while in the hospital and if that differs across floors that have or have not deployed a nursing mobility protocol. We will also explore changes in patient functional decline and 30-day hospital readmission.

## 3. Aims

### *3.1 Primary outcome*

The primary outcome variable is the change in mean daily step count from the baseline period (week 1 post-discharge) to the intervention period (weeks 2-13 post-discharge).

### *3.2 Secondary outcome*

The secondary outcome variables are functional decline from admission to 3-months post-discharge and 30-day hospital readmission.

## 4. Background

Hospitalization is a common occurrence for older adults; approximately 6.8 million Medicare seniors experience an admission for acute care in any given year.(1,2,3) This is often a sentinel event in the overall health trajectory of older adults that is complicated by functional impairment, (4,5) Skilled Nursing Facility placement, (6,7) and reduced mobility after discharge.(8)

In the current paradigm, low mobility during hospitalization is largely viewed as a temporary inconvenience that should not affect overall functional ability or outcomes such nursing home placement and that patients should return to their previous activity level soon after they return home without lingering mobility changes. Recent research, however, suggests disruptions of basic activities of daily life such as mobility (getting out of bed and walking) may be

"traumatic"(9) or "toxic"(10) to older adults with long-term post-hospital effects.(11) What we lack is precise data on how much immobility is noxious and how much mobility is needed to protect against adverse outcomes.

2. AARP Public Policy Institute. The Medicare Beneficiary Population Fact Sheet. Accessed online on February 17, 2016 at: [http://assets.aarp.org/rgcenter/health/fs149\\_medicare.pdf](http://assets.aarp.org/rgcenter/health/fs149_medicare.pdf)

3. The Dartmouth Atlas of Health Care. Hospital Discharges per 1,000 Medicare enrollees. Accessed online on February 17, 2016 at: <http://www.dartmouthatlas.org/data/topic/topic.aspx?cat=19>

## Study design

### *5.1 Design*

We will conduct a two-arm randomized, controlled trial during the 3-months after hospital discharge comparing a control group that uses a wearable device to track physical activity to an intervention group that uses the same wearable devices and receives a supportive social incentive-based gamification intervention to adhere to a step goal program. Patients will be enrolled during hospitalization from medicine and oncology floors into three phases. In phase 1 (hospitalization), patients' inpatient step counts will be monitored. In phase 2 (week 1 post-discharge), patients will have a baseline step count estimated. In phase 3 (weeks 2-13 post-discharge), patients will be randomly assigned to the control or intervention group. Patients will be considered enrolled in the trial if they complete the run-in periods (phases 1 and 2) and then are randomized into phase 3.

The enrollment phase will be part of another randomized trial (The RETAIN study) which evaluates how the magnitude of financial incentives impacts patient enrollment. This trial will be completed and unmasked to patients before they begin the phase 1 of our study.

### *5.2 Study duration*

The study will begin in Winter 2018. The primary intervention period is the 3-months post-hospital discharge. We expect the entire study to take approximately two years to conduct and analyze outcomes.

### *5.3 Target population*

Adults age 18 years or older who are admitted for inpatient care to the Hospital of the University of Pennsylvania (HUP) on medicine or oncology floors.

### *5.4 Accrual*

We will aim to enroll and randomize 300 patients. We estimate that a sample size of at least 300 participants (150 per arm) will provide 90% power to detect a difference of 700 steps in the change in mean daily step count from baseline to the intervention period between intervention and control, using a 2-sided  $\alpha$  of 0.05, assuming a baseline mean step count of 5000 steps in the control group with a standard deviation of 2500 steps, and accounting for a 10% dropout rate.

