## **9. Analysis plan**

In our primary analyses, we will multiple imputation for missing data and use linear mixed effects models to compare the change in mean daily step count from baseline to 12-week intervention period, adjusting for baseline step count and time. To test of the robustness of our findings we will also evaluate models using collected data without imputation. All hypothesis tests will be two-sided using a two-sided alpha of 0.05 as our threshold for statistical significance. In secondary analyses, we will evaluate how differences in inpatient and changes in post-discharge step counts are associated with secondary outcome measures.

In exploratory analyses, we will compare how differences in hospital mobility protocols are associated with differences in step counts. We will also conduct a qualitative analysis to evaluate participant perceptions of the intervention.

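### The 90% power in Protocol 5.4 cannot be reproduced from the inputs listed there; it needs an SD of change, or a baseline-to-follow-up correlation, that the protocol does not state

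*Protocol*

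**What the plan says.** Section 5.4 (Accrual) states that "at least 300 participants (150 per arm) will provide 90% power to detect a difference of 700 steps". The target is "a difference of 700 steps in the change in mean daily step count from baseline to the intervention period between intervention and control", so the powered quantity is a between-arm difference in change. The spread is introduced by "assuming a baseline mean step count of 5000 steps in the control group with a standard deviation of 2500 steps", and the sentence ends by "accounting for a 10% dropout rate". Section 5.4 sets alpha at 0.05 two-sided, and section 9 (Analysis plan) agrees: "All hypothesis tests will be two-sided using a two-sided alpha of 0.05".

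Section 3.1 defines the primary outcome as the change from week 1 after discharge to weeks 2-13. Section 9 plans a linear mixed model adjusted for baseline steps, with multiple imputation. Nowhere does the protocol give an SD of the change or a correlation between baseline and follow-up steps. Section 5.4 also does not say that its power figure relies on the baseline adjustment.

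**The concern.** A sample-size statement should let a reader recover its power from its own inputs. Here the inputs look complete: size, difference, SD, alpha and dropout. Put into the usual two-sample formula, they miss the stated power by about 27 percentage points, too much to put down to rounding or to the choice between a normal and a t calculation.

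The SD is also attached to a different quantity from the one being tested. Power for a difference in change depends on the SD of the change, or on the residual SD after baseline adjustment. Either one depends on how strongly baseline and follow-up steps are correlated. That correlation decides whether the 90% is right, and it is absent.

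At stake is how a null primary result is read. A reader who trusts 90% power would treat a null as fairly strong evidence against a 700-step effect. Whether that is justified depends on an assumption that the reader cannot see.

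**Working it through.** **Inputs.** From section 5.4: 150 per arm, difference 700, SD 2500 (worded as the SD of the baseline count), alpha 0.05 two-sided, dropout 10%. Completers per arm: 150 × 0.9 = 135. The calculations use a two-sample t-test with equal arms.

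**1. Attempt to reproduce the 90%, using 2500 as the SD of the analysed outcome.**

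SE = SD × √(2/n) = 2500 × √(2/135) = 304.3. Ratio = 700/304.3 = 2.30.

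- 135 per arm: power 63.0% (normal approximation 63.3%).
- 150 per arm, no dropout: SE 288.7, ratio 2.42, power 67.6% (67.9%).
- One-sided alpha of 0.05, as a check on other readings (normal approximation): 74.4% at 135 per arm and 78.2% at 150.

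None of these reaches 90%.

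**2. What SD 2500 would support.** By the normal approximation, n per arm = 2 × (1.960 + 1.282)² × 2500²/700² = 268.05, so 269. The t-test needs just over 269, so 270. Dividing by 0.9 gives 270/0.9 = 300 per arm.

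With 135 per arm, 90% power needs a ratio of about 3.253. The detectable difference is then 3.253 × 304.3 ≈ 990 steps (986 by the normal approximation).

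**3. What would make the 90% correct.** At 135 per arm the SD must be 700/(3.253 × √(2/135)) ≈ 1768 (1774 by the normal approximation). Assuming equal variances at baseline and follow-up:

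- Change score, SD = 2500 × √(2(1−r)): r = 1 − (1768/2500)²/2 = 0.75.
- Baseline-adjusted, SD = 2500 × √(1−r²): r = √(1 − (1768/2500)²) = 0.71.

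**4. Power at 135 per arm for assumed correlations.** The protocol gives none, so these are illustrations.

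| Assumed r | SD, change score | Power | SD, baseline-adjusted | Power |
|---|---|---|---|---|
| 0.3 | 2958 | 49% | 2385 | 67% |
| 0.5 | 2500 | 63% | 2165 | 75% |
| 0.6 | 2236 | 73% | 2000 | 82% |
| 0.7 | 1936 | 84% | 1785 | 89% |
| 0.75 | 1768 | 90% | 1654 | 93% |
| 0.8 | 1581 | 95% | 1500 | 97% |

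The 63% in step 1 is therefore the r = 0.5 case for a change score, or the r = 0 case for a baseline-adjusted analysis.

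**The case against.** The strongest reply is that 2500 was never offered as the SD of the change. Section 5.4 attaches it to the baseline count, section 9 adjusts for baseline, and section 8.2 stratifies the randomisation on baseline steps. For a baseline-adjusted analysis, 63% is the value with no gain at all from the adjustment, which is the least natural reading. Baseline is a one-week mean and follow-up a 12-week mean, and nothing in the protocol rules out a correlation near 0.7 between two such averages. Multiple imputation also means that dropouts are not simply discarded. With no loss at all, the required SD rises to about 1864, and the required correlation falls to 1 − (1864/2500)²/2 = 0.72 for a change score or √(1 − (1864/2500)²) = 0.67 with adjustment.

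Much of this stands. A reader might infer that the true power is 63%, so that a real 700-step effect would be missed 37% of the time instead of 10%. The protocol does not support that as a flat statement, because it holds only if the analysed SD is 2500.

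A reader might also infer that a per-arm figure was entered as the total, since step 2 returns 300 per arm. That is one possibility. A one-sample formula, which drops the factor of 2, gives 134.02/0.9 = 148.9, which also matches 150 per arm. So does a legitimate calculation with r of about 0.71 to 0.75. The document cannot tell these apart, and a mix-up should not be asserted.

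The reply does not rescue the statement as written. It shows that 90% is possible, not that it follows from what is listed. Baseline here is the first week home from hospital, so a correlation of 0.7 or more with the following 12 weeks has to be stated and justified. The imputation point is minor: imputation does not restore full information, and section 5.4 itself claims to allow for dropout.

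**Conclusion.** The point holds as a statement that the claimed power is unsupported. The 90% cannot be reproduced from section 5.4's own inputs, and no other section supplies what is missing. The size of the gap depends on the missing input. At 135 completers per arm, power is about 63% if the analysed SD is 2500. Over assumed correlations of 0.5 to 0.7 it runs from 63% to 84% for a change score and from 75% to 89% with baseline adjustment. It reaches 90% only at about 0.75 or 0.71 respectively.

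These figures assume equal variances at the two times, equal arms, and a comparison of arm means that stands in for the planned mixed model. The finding does not establish that the trial is underpowered, or how the mismatch arose. It is nonetheless worth correcting before results are read, because the figure supports the primary outcome and is a statement that the protocol itself makes, not a detail left for an SAP.

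**What to change.** Keep the sample size at 300 and restate section 5.4.

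- **If an SD of change or a correlation was used:** state it, say where it comes from, and match it to the baseline-adjusted analysis in section 9. Give the resulting power at 135 per arm and a short sensitivity table over plausible correlations, such as the one above.
- **If none was used:** replace the 90% with what SD 2500 gives, namely about 63% power for 700 steps, or 90% power for about 990 steps. Label it as conditional on 2500 being the SD of the analysed outcome.

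In both cases, say explicitly whether 2500 is the SD of the baseline count or of the change.

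The cost is wording in one section. Recruitment, procedures and analysis do not change. The price is that the stated power or detectable difference becomes less favourable unless a correlation of about 0.71 (baseline-adjusted) or 0.75 (change score) can be justified.

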### *5.5 Key inclusion criteria*

1) Age 18 years or older; 2) admitted to medicine or oncology floor in the hospital

### *5.6 Key exclusion criteria*

1) Inability to provide informed consent; 2) does not have daily access to a smartphone compatible with the wearable device and not willing to use a device that we can provide them; 3) already enrolled in another physical activity study; 4) inpatient mobility score of 0 or 1 indicating that physical activity is not appropriate for the patient; 5) any other medical conditions that would prohibit participation in an 3-month physical activity program; 6) unable to complete the run-in phases (e.g. not discharged from the hospital within 60 days of enrolling in the study; not willing to use the wearable device for the 3-month post-discharge intervention)

## **6. Subject recruitment**

### *6.1 General*

The study team will use the electronic health record to identify potentially eligible patients in the hospital. The enrollment portion of the study will be conducted using the protocol from the RETAIN study.

### *6.2 Populations vulnerable to undue influence or coercion*

Not applicable

## **7. Subject compensation**

Participants will receive \$150 for enrolling and \$150 for completing the 3-month post-discharge period.

## **8. Study procedures**

### *8.1 Consent*

Using a REDCap survey module on a tablet, the clinical research coordinator will read a pre-MOVE IT consent script (see Script 2\_Pre-MOVE IT Consent Intro Script) and proceed to present the MOVE IT informed consent/ HIPAA forms with additional information regarding the RETAIN incentive randomization condition. Participants will be able to progress through the consent form at their own pace, as well as review the consent form on one full page at the end on the tablet. REDCap will capture the time spent reading the individual sections of the consent form, which will be featured as images.

Once participants finish reading the electronic version of the MOVE IT consent form with randomized compensation information, they will hand the tablet back to the clinical research coordinator.

The clinical research coordinator will then toggle back to the Way to Health in order to present the next set of surveys. Patients will then complete brief assessments of perceptions of research risk, perceptions of the difference between research and individualized patient care, and understanding of the MOVE IT study via a trial elements quiz (please see Attachments RETAIN\_1 through RETAIN\_9 surveys). Patients' advancement through the consent process

will not be contingent on their responses to the quiz; however, following completion of the quiz, research coordinators will review the questions that patients missed and discuss these portions of the consent until the participant understands the entire consent and its detailed procedures.

Participants will be provided with the paper consent form for signature and will be asked to either provide consent or decline participation in the parent trial (MOVE IT). In the paper copy of the consent, details regarding how to contact the research team via email or phone will be provided in the event a participant wants to withdraw from the study.

As part of the collaboration with RETAIN, we seek approval to alter the required elements of the informed consent process in order to temporarily withhold information regarding the randomization to one of three incentives for research participation. All patients who consent to MOVE IT will be debriefed in the same encounter during which they were approached. Please see Script\_3\_Debriefing Script\_RETAIN\_MOVE IT, which includes the following information:

- Clinical research coordinator will describe the study's use of deception and purpose.
- Patients will also be informed of payment equalization (e.g. all participants will receive a \$300 incentive amount in two payments.
- Patients will be asked if they would like to receive their payment.
- In order to receive their payment of \$300 in two installments (\$150 to be processed immediately and \$150 during once their 3-month follow-up for MOVE IT is complete), participants may be asked to complete a W-9.

## *8.2 Procedures*

Each day, the research coordinator will use an electronic health record query to generate a list of patients that are admitted to medicine and oncology floors and meet AMPAC and age requirements. At enrollment, the research coordinator will administer two additional screening questions to determine eligibility (owns a smart phone and not in another physical activity study) via the RedCap portal. If the participant successfully passes the screening questions, the patient can be consented to the study. The research coordinator will next present a series of to the patient to be completed through the Way to Health portal. These instruments include: the Pittsburgh Sleep Quality Index, Karolinska Scale, Activity of Daily Living-Instrumental Activities of Daily Living Survey, Life Space Activity Survey, Mini-Nutritional Assessment Survey, Edmonton Symptom Assessment Survey, Treatment Burden Questionnaire, Lubben Social Network Scale, Self Rated Health Survey, and Dementia Tool.

After completing the enrollment assessment, the research coordinator will show patients how to use the wearable device which can be worn on wrist (like a watch), carried in any pocket, or clipped to hospital gown. After they are enrolled, participants will receive a daily text message

with a link to complete two surveys in Way to Health about their sleep quality and symptom assessment for up to 10 days of hospital admission, or until they are discharged.

Upon hospital discharge, there will be a one-week run-in period after discharge to estimate baseline step counts for all patients. After week 1, all participants will be notified to complete post-discharge baseline surveys. For all patients with a baseline step count, they will be randomly assigned to control or intervention using block sizes of two and stratifying on baseline step count (<5000 daily steps, 5001 to 7500, or > 7500) and hospital admission floor.

Participants in the control group will continue to have data collected passively. Participants in the control arm will only receive study communications when it is time for them to complete surveys in the Way to Health system.

Participants in the intervention arm will have a weekly step goal that increases from baseline by 10% each week of the intervention (12 weeks) with a maximum of 10,000 steps. At the beginning of each week, the participant receives 70 points (10 points for each day that week). If the participant does not meet their step goal, they lose 10 points from their balance. This leverages loss aversion, which has been demonstrated to motivate behavior change more effectively with losses than gains. At the end of each week if the participant has at least 40 points, they will move up a level (levels from lowest to highest: blue, bronze, silver, gold, platinum). If not, the participant will drop a level. All participants begin at the silver level. Each week, participants get a fresh set of 70 points on Monday. Participants will receive daily feedback for the step counts, and weekly feedback for their levels. Participants in the intervention arm will be asked to identify a family member or friend to be their support sponsor. A weekly report will be sent to this person with the participant's performance (points and level).

Participants in both arms will also receive a notification when it is time to complete surveys in the Way to Health system (5, 9, and 13 weeks after hospital discharge). 3 days after the surveys are sent to participants, a message will be sent reminding them to complete the surveys if they have not already done so. Upon completion of the final set of surveys, \$150 will be processed for participants in both arms.

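### Fixed blocks of two, with visibly different arms, let anyone who holds the block size and earlier allocations foresee half of all assignments

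*Protocol*

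**What the plan says.** - **Block size (8.2 Procedures).** Patients are "randomly assigned to control or intervention using block sizes of two". No other size, and no random variation in size, is given.
- **Strata (8.2).** The list is built "using block sizes of two and stratifying on baseline step count (<5000 daily steps, 5001 to 7500, or > 7500") and by hospital admission floor. The number of floors is not stated.
- **Ratio (5.4 Accrual).** The target is "a sample size of at least 300 participants (150 per arm"), so allocation is 1:1.
- **How the arms look (8.2).** In the intervention arm, "Participants will receive daily feedback for the step counts, and weekly feedback for their levels", and a support sponsor gets a weekly report. By contrast, "Participants in the control arm will only receive study communications when it is time for them to complete surveys". The protocol does not use the term open-label, but it describes no masking of arm for patients or staff.
- **Timing (5.1 Design).** "Patients will be considered enrolled in the trial if they complete the run-in periods (phases 1 and 2) and then are randomized into phase 3". Consent is taken in hospital (8.1), the baseline week follows discharge, and allocation comes after that.
- **Grounds for not going forward (5.6 Key exclusion criteria).** These include other medical conditions that prohibit participation and inability to complete the run-in. One example given of the latter is a patient "not willing to use the wearable device for the 3-month post-discharge intervention".

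**The concern.** Two is the smallest possible block and the most predictable one. Where earlier assignments can be seen, the next can often be foreseen. If any judgement is then left about whether or when a patient is randomised, foreknowledge can shape who enters which arm. Bad faith is not needed: chasing a missing device sync harder for one patient than for another would be enough.

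The primary outcome is change in daily steps, which plausibly depends on motivation and willingness. The primary model in section 9 adjusts for baseline step count and time. That would absorb selection on measured baseline activity, but not selection on motivation or frailty beyond it.

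Separately, the printed step strata do not meet at 5000.

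**Working it through.** The protocol gives no figure for predictability, so there is none to reproduce. The inputs are block size 2 and the strata (8.2), 1:1 allocation of 300 patients (5.4), and a baseline mean of 5000 with SD 2500 (5.4). My assumptions are a normal shape for baseline steps and 1 to 12 floors, giving 3 to 36 strata.

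**1. Assignments fixed in advance.** A 1:1 block of size 2m has an expected share 1/(m+1) of assignments forced by those before it. For m = 1 this is 1/2 = 50%.

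**2. Best-guess success.** The observer guesses the arm that is behind and tosses a coin when the arms are level. Expected correct guesses per block are m + (4^m / C(2m, m) − 1)/2.

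| Block size | Forced | Correct guesses |
|---|---|---|
| 2 | 1/2 = 50% | [1 + (4/2 − 1)/2]/2 = 75% |
| 4 | 1/3 = 33.3% | [2 + (16/6 − 1)/2]/4 = 70.8% |
| 6 | 1/4 = 25% | [3 + (64/20 − 1)/2]/6 = 68.3% |

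**3. What the observer must know.** The last allocation alone is not enough. With probability 1/2 the next patient completes a pair and the arm is certain. With probability 1/2 a new pair begins and it is an even chance. The next arm is then the opposite one with probability 1/2 × 1 + 1/2 × 1/2 = 75%. Certainty needs the block size and the position in the block, which means the earlier allocations in that stratum.

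**4. Incomplete blocks.** With k strata, about half end on an odd count, so the forced number is about (300 − k/2)/2. This gives 149 for k = 3 and 141 for k = 36, or 50% down to 47% of 300. Simulation over the assumed floors agrees (149.2 and 141.0).

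**5. Randomly varying blocks.** I simulated sizes 2, 4 and 6 chosen with equal chance. Best-guess success is about 69% in strata of 12 to 25 patients and about 70% in strata of 100. If the sizes are not known, no assignment is certain. If they leak, some are:
- An imbalance of three forces the next assignment, which happens for about 0.8% of assignments.
- An observer who follows the whole sequence can do better. For example, AABA at the start of a stratum can only be a block of 6, so the next two are B. By simulation, about 3% to 4% of assignments are then certain, against 50% under blocks of two.

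**6. Balance given up.** The largest possible within-stratum difference between arms is half the largest block: 1 patient with blocks of two, 3 with blocks up to six.

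**7. The gap in the strata.** A mean of exactly 5000, or a fractional mean below 5001, falls in no stratum. The 7500 cut has no gap. P(5000 ≤ X < 5001) = Φ(1/2500) − Φ(0) = 0.00016, and 300 × 0.00016 ≈ 0.05 patients.

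**The case against.** The strongest reply is that the usual route to selection bias is largely shut. Patients consent in hospital, and the step stratum comes from device data collected afterwards, so a recruiter cannot know the stratum of the patient being approached. Section 8.2 then randomises all patients with a baseline step count, which reads as a data-driven trigger. Unwillingness to wear the device is the patient's own decision, and discharge within 60 days is objective. This stands, and it narrows the risk considerably. What it leaves open is judgement at the end of the run-in: section 5.6 gives its run-in failures only as examples, section 8.2 does not say what makes a baseline count usable, and section 11.5 has the coordinator and investigator review events to decide whether a participant continues.

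Second, the protocol does not say who can see earlier assignments. That also stands: staff access is an inference from visibly different arms. Central list generation and system locks are commonly set out elsewhere, so their absence here is not a fault.

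Third, small blocks protect balance when 300 patients are spread over many strata. This is a fair reason for the choice, but the balance given up is small (step 6).

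Fourth, moving from 75% to about 69% is a modest gain. It is. The larger gain is in certainty, and that depends on keeping the sizes undisclosed.

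A reader might infer that knowing the last allocation always reveals the next, or that staff could choose whom to recruit by foreseen arm. Step 3 rules out the first. The order of consent, run-in and stratification largely rules out the second.

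**Conclusion.** The stated rule makes 50% of assignments in complete blocks fully determined and 75% guessable, for someone who knows the block size and the stratum's earlier allocations. Over an assumed 3 to 36 strata, that is about 149 down to 141 of 300 patients. These figures follow from section 8.2 alone. That the foreknowledge could be used rests on two inferences: that staff who handle run-in completion can see earlier assignments, and that some discretion remains at that point.

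The documents do not show that selection occurred, nor that staff held the block size or tracked the sequences. The point is a worthwhile, low-cost improvement to a design choice, not a demonstrated bias. The strata gap is a clerical slip with negligible effect.

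**What to change.** In section 8.2, replace the fixed block size with randomly varying permuted blocks (for example 2, 4 and 6), and state that the sizes are not disclosed to staff who handle run-in completion. The actual sizes should then be kept out of the protocol copy those staff hold.

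In the same edit, print the step strata as ≤5000, >5000 to 7500, and >7500.

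The cost is a new randomisation list and a sentence or two of text. The within-stratum difference between arms could reach 3 patients rather than 1, which matters most if there are many floors and small strata. Adjustment for baseline steps, already planned, covers part of that.
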